#### Baseline survey

Participants will complete a baseline survey that captures detailed information about demographic characteristics, place of birth, acculturation based on language (if appropriate), family structure, comorbid conditions, occupation/industry, work environment and job tenure, job tasks, union membership, and income (household and individual), which will be analyzed as a function of the federal poverty level to account for household size and secular trends [8, 52, 53]. Financial worry and distress will be assessed using the 12-item Comprehensive Score for financial Toxicity (COST). The baseline assessment will also include an assessment of symptoms using the National Cancer Institute PRO-CTCAE® and of perceived efficacy in patient-physician interactions (5-item PEPPI) [54, 55]. These measures will be combined with the measure of self-efficacy to ask an employer for accommodations (which was assessed at the time of eligibility determination). All measures used are from existing instruments that have been validated (either externally or by members of the research team) and translated into Spanish using standard methods [56].

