#### On-treatment surveys

To limit participant burden, on-treatment surveys will be completed at approximately the mid-point of chemotherapy and with the last cycle only. Although the time between surveys will vary based on the regimen prescribed, the number of surveys administered to each participant will not vary. Participants whose chemotherapy regimen changes after treatment initiation will be surveyed at the projected mid-point of the regimen (on average 5–10 weeks). Such a change in adjuvant treatment regimen is rare and is not expected to affect study results. Moreover, detailed treatment information will be captured, and any effect of such a change will be evaluated in sensitivity analyses. These surveys will include an assessment of symptoms, accommodations, work status, and the two measures of self-efficacy (to ask an employer for accommodations and in patient-physician interactions).

Symptom control will be assessed using the NCI’s PRO-CTCAE®, which has been validated in English and Spanish [57, 58]. The scale may be used to measure symptoms over a period of anywhere between 1 day and 4 weeks [59]. Standard chemotherapy regimens for breast cancer have cycles varying in length from 1 to 3 weeks. Therefore, we will ask each patient to recall symptoms over the duration of the period since the last cycle of treatment. For example, if a patient is receiving chemotherapy on a 2-week cycle, her surveys will refer to her experience of symptoms over the course of the preceding 2 weeks. However, if she is receiving treatment on a 3-week cycle the questions will refer to the preceding 3 weeks.

Receipt of workplace accommodations will be assessed by asking participants about the kinds of accommodations they have requested, and whether these have been granted, including if the request was granted in full, in part, not at all, or if something else was offered in its place. Work will be measured in terms of employment status, work hours, and participant choice regarding these outcomes. Additional assessments will include self-efficacy to ask for accommodations and in patient-physician interactions.

Self-efficacy to ask for accommodations will be measured using a 5-item tool that we have developed and validated for this purpose (manuscript in preparation).

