Aim 3: To evaluate the effect of the TEAMWork App on confidence in asking an employer for accommodations and on receipt of accommodations during and after adjuvant therapy.

*Analysis:* The relationship between the app and confidence asking for accommodations at the mid-point of chemotherapy and 4 months post-treatment will be evaluated using chi-squared tests. In subset analyses, the relationship between job retention and receipt of accommodations will be evaluated among participants who asked for accommodations.

Aim 4: To evaluate the effect of the TEAMWork App on patient efficacy in communicating with the provider and self-reported symptom burden during and following adjuvant therapy.

*Analysis:* Participants randomized to receive the app are hypothesized to have higher efficacy in communicating with the provider and lower symptom burden during and after treatment than those randomized to the informational booklet. Perceived efficacy in patient-physician interactions as measured by the PEPPI score will be compared by arm using the 2-sample *t*-test [22]. For each symptom, we will compare symptom incidence and severity by study arm. To compare symptoms, we will conduct 2 sets of analyses. One will compare the rate of symptom incidence by assigned study arm at the mid- and end-of-chemotherapy-treatment time-points separately. A second analysis will report an arm comparison of whether patients who reported a symptom at the mid-treatment survey experienced an increase, decrease, or cessation of that symptom at the end of chemotherapy treatment. The main analytic tool that will be used for these analyses is the chi-squared test.

Exploratory aim 1: To evaluate the effect of the TEAMWork App on treatment adherence.

*Analysis:* We will compare treatment adherence (RDI) by receipt of the app in a Wilcoxon rank sum test.

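### Aim 4's symptom-change comparison, the only described one that uses severity, is confined to women symptomatic at mid-treatment, so it is not a randomised comparison

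*Protocol article*

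**What the plan says.** The Aim 4 paragraph of *Statistical methods for primary and secondary outcomes {20a}* opens with a general intention: "For each symptom, we will compare symptom incidence and severity by study arm". It then sets out two analyses.

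- First analysis: "One will compare the rate of symptom incidence by assigned study arm at the mid- and end-of-chemotherapy-treatment time-points separately".
- Second analysis, on change between the mid-treatment survey and the close of chemotherapy: the arms are compared on "whether patients who reported a symptom at the mid-treatment survey experienced an increase, decrease, or cessation of that symptom".

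On the method it adds: "The main analytic tool that will be used for these analyses is the chi-squared test". The hypothesis is that women given the app will have "lower symptom burden during and after treatment than those randomized to the informational booklet".

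Two other sections matter. Under *Baseline survey*: "The baseline assessment will also include an assessment of symptoms using the National Cancer Institute PRO-CTCAE". Under *On-treatment surveys*: "we will ask each patient to recall symptoms over the duration of the period since the last cycle of treatment". *Outcomes {12}* lists symptom burden as a secondary endpoint.

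**The concern.** The app is meant to improve symptom control during treatment. Whether a woman reports a symptom at mid-treatment is therefore partly a result of her allocation. If the app prevents or delays symptoms, it removes women from the second analysis, and those removed need not resemble those who stay. The remaining app and control women are not comparable by design, and a difference between them mixes the effect of the app with this selection.

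The stake is the severity result for a named secondary endpoint. The first analysis records presence only, so every statement about severity would come from the second. Severity is promised by arm, but no described analysis compares it in all randomised women.

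A smaller point concerns the first analysis. Each on-treatment survey asks about the time since the last cycle, so presence at a survey is a period prevalence. As worded, the analysis calls this incidence and makes no use of the baseline PRO-CTCAE.

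**Working it through.** **1. The plan's only Aim 4 figure.** It concerns PEPPI: 38 v 42, SD 12, 167 per arm, two-sided 5%, stated power above 85%. SE = 12 × √(2/167) = 1.313; 4/1.313 = 3.046; Φ(3.046 − 1.960) = 0.861. It reproduces. No figure is stated for symptoms, so every symptom rate below is an assumption.

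**2. Applying the rules as written** (grade at mid → grade at end):

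| Trajectory | First analysis | Second analysis |
|---|---|---|
| 0 → 3 (new, severe) | absent at mid, present at end; grade not used | not in the set |
| 2 → 2 (unchanged) | present, present | in the set, no named category |
| 1 → 0 | present, absent | cessation (correct) |

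**3. Can the second analysis point the wrong way?** Assume a latent normal severity at mid and at end with correlation ρ = 0.5, 0.6 or 0.7. A symptom is present above 0 and grades 1–4 start at 0, 0.5, 1.0 and 1.5, so control prevalence is 50% at both surveys. The app shifts the latent mean down by 0.3 SD, which gives a prevalence of Φ(−0.3) = 38.2% wherever it acts. Cell probabilities come from the bivariate normal distribution. Hand check for controls at ρ = 0.5: P(present at mid, absent at end) = 1/4 − arcsin(0.5)/2π = 0.1667, and 0.1667/0.5 = 33.3% cessation.

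Percentages among women symptomatic at mid-treatment, for ρ = 0.5 / 0.6 / 0.7:

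| | Increase | Cessation |
|---|---|---|
| Control | 22.5 / 23.1 / 23.3 | 33.3 / 29.5 / 25.3 |
| App, 0.3 SD at mid, none at end | 29.4 / 31.6 / 34.1 | 29.2 / 24.6 / 19.5 |
| App, 0.3 SD at mid, 0.2 SD at end | 22.5 / 23.9 / 25.2 | 37.3 / 32.5 / 27.2 |
| App, 0.3 SD at both | 19.4 / 20.4 / 21.2 | 41.5 / 36.8 / 31.6 |

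In the second row the app arm is better at mid (38.2% v 50%) and equal at the end (50% v 50%), yet it shows more increase and less cessation. In the last row the direction is right. The third row is near neutral on increase and favours the app on cessation.

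In controls, new onset after mid-treatment is 16.7 / 14.8 / 12.7% of all women and 60 / 56 / 52% of all worsening from mid to end. The second analysis scores none of it. Of the control women it does score, 21.6 / 24.3 / 28.0% are unchanged.

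**4. A different model.** Control: 40% have a transient symptom at mid (60% cease, 10% increase), 20% a persistent one (10% cease, 40% increase), and 40% none (30% new onset by the end). The app prevents half of the transient symptoms and cuts new onset to 20%.

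- Control, second analysis: cessation (0.4×0.6 + 0.2×0.1)/0.6 = 43%; increase (0.4×0.1 + 0.2×0.4)/0.6 = 20%.
- App, second analysis: cessation (0.2×0.6 + 0.2×0.1)/0.4 = 35%; increase (0.2×0.1 + 0.2×0.4)/0.4 = 25%.
- Prevalence, control v app: 60% v 40% at mid; 46% v 38% at end.

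The app is better at both surveys and looks worse in the second analysis, because the symptoms it prevented were the ones likely to cease. Here too the benefit is larger at mid (20 points) than at end (8 points).

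**5. Would adding new onset to the change table be enough?** Not in general. In the model of step 4, worsening in all women is 24% control v 22% app, so the reversal goes. In the mid-only scenario of step 3, worsening from mid to end in all women is still 34.2 / 33.3 / 32.3% app v 27.9 / 26.3 / 24.3% control, simply because the app arm started lower. Change from mid to end is a poor basis for an arm comparison; grade at each survey is not.

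**6. Baseline symptoms in the first analysis.** If a share b has a persistent baseline symptom in both arms and true new onset is 50% v 35%, the observed difference is (1 − b) × 15 points: 15, 13.5, 12 and 10.5 points for b = 0, 10, 20 and 30%. Power at 167 per arm is 79, 70, 60 and 50%. The difference shrinks but keeps its sign.

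**The case against.** The strongest reply has four parts.

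- *New onset is not lost from the plan.* A reader might infer that worsening by new onset is never counted. That is wrong: a woman who first has the symptom at the end of chemotherapy is a case in the first analysis at that time-point. What is lost is her grade, and her place in the change comparison.
- *The reversal depends on the scenario.* With an equal effect at both surveys the second analysis points the right way, and nothing in the documents says that the benefit will fade; non-use reminders run for 8 months, by when most women will have finished chemotherapy. This stands and limits the claim to what can happen. It does not restore the randomised comparison, which is lost whichever way the result falls. Even in the adverse case the first analysis would show the app better at mid-treatment, so the harm signal would not stand alone.
- *Baseline symptoms.* A reader might infer that counting them could make an effective app look harmful. It cannot: under randomisation the first analysis is unbiased between arms, and the cost is dilution. That baseline is ignored is also read from silence, and a fuller analysis plan could define it.
- *Detail belongs in the analysis plan.* This is fair for the unchanged category, an obvious residual cell, and for the choice of model. It does not cover the restriction to women symptomatic at mid-treatment, which the article itself states for an arm comparison.

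**Conclusion.** The point holds for the second symptom analysis. As written, it compares arms within a subset defined by a post-randomisation outcome, omits onset after mid-treatment, names no unchanged category, and is the only described use of severity. Under the assumed rates it can show *increase* about 6.9 to 10.8 points higher (29.4 − 22.5; 34.1 − 23.3) and *cessation* about 4.1 to 5.8 points lower (33.3 − 29.2; 25.3 − 19.5) in an app arm that is never worse at any survey. This needs a benefit that is mainly early. The sizes rest wholly on assumed prevalence, correlation and effect; the loss of the randomised comparison does not.

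The first analysis is a valid comparison by assigned arm. Its faults are a label (prevalence called incidence) and, as worded, an unused baseline. The documents do not support reading the whole Aim 4 symptom plan as biased against the app. The scope is one secondary endpoint; the primary endpoint's arm comparison is untouched.

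**What to change.** Make the severity comparison the PRO-CTCAE grade at mid-treatment and at end of chemotherapy, with absent scored 0, in all randomised women with a survey, by assigned arm. Use an ordinal or linear model adjusted for baseline grade and the stratification factors (language and recruitment site).

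Keep the mid-to-end table as description only. Tabulate all women, with the categories never, new onset, increase, unchanged, decrease and cessation, and draw no arm inference from it. Call presence at a survey prevalence, or reserve incidence for women free of the symptom at baseline.

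The cost is wording: all the data are already to be collected. The small downside is a model in place of a chi-squared test, with a stated rule for women who have no baseline grade.

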### Interim analyses {21b}

We have incorporated monitoring and a standalone early stopping rule to ensure the app is not causing harm. Overall, approximately 6% of BCW study [7] participants said they thought their employer had treated them unfairly. In the current study, we will call each participant who takes the 4-month survey and says her employer treated her unfairly, and we will ask about the circumstances that led to this negative outcome. Any staff making such calls will undergo sensitivity training to ensure the participant is not subject to coercion or the perception thereof as a result of the call. If there are 10 cases (per arm, at any time during the study) for whom the negative outcome is attributable to the app or booklet, we will stop the study. During the monitoring process, we will revise the intervention as needed.

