In BCW [7], approximately 50% of pre-diagnosis employed women who underwent chemotherapy were working 4 months after treatment completion. The difference in outcome between participants who did and did not have access to paid sick leave through their jobs was approximately 19% and was statistically significant (*p*=0.01). The mechanism of action of our intervention is hypothesized to be that working during the treatment period will provide job security to women and, therefore, lead to long-term job retention. Because paid sick leave provides similar job security, we will use a conservative effect size of 15% for our proposed intervention.

To identify an improvement of 15% in job retention 4 months post-treatment (i.e., 65% job-retention) in the arm randomized to receive the app, we would require 167 evaluable participants in each arm based on a 2-sided test with a 5% type I error and 80% power. We plan to recruit 420 women to obtain primary outcome data from 334 participants (assuming >80% retention 4 months post-treatment). *As noted above, we have estimated 80% retention 1 year post-treatment; we anticipate having higher retention 4 months post-treatment. Thus, we will have at least 80% power and 5% type I error to detect improvements in job-retention of 15% or more 1 year post-treatment. We expect further attrition by year 2. With a conservative 60% retention rate at 2 years, we will have 80% power to detect a difference of at least 17% for job retention at year 2. Using mixed models and important covariates, the detectable effect size for this comparison will likely decrease.*

*Sample size for sub-aim 1:* Characteristics of interest include chemotherapy regimen, symptom burden, race/ethnicity, language, and job tasks. We anticipate that, for example, 35% of participants in the study will have jobs that involve standing for long periods of time. This distribution will allow us to determine whether the association between the app and job retention varies by this job task.

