Each of these specific risks is addressed below.Repercussions if an accommodation is requested and denied*Psychological repercussions*: Participants who request accommodations at work but are denied these may find that their self-efficacy to ask for accommodations decreases rather than increases as a result. A similar outcome could occur if their attempts to improve communication with the clinic team (e.g., a request for a more potent antiemetic or for a letter to take to the employer) are not well received. All research staff will be trained to identify signs of psychological discomfort in the participants. Any patient reporting significant distress (or indicating distress through other signs) will be referred to a licensed or board-certified mental health provider for additional evaluation, support, and/or referrals as needed.*Work-related repercussions:* Participants who report that they have experienced negative work-related repercussions of study participation will be referred to counseling and/or pro bono legal services, as appropriate and based on participant preferences. Moreover, we have incorporated an early stopping rule into the proposal, based on this potential adverse outcome. Additional details are included in the research plan and in the Data and Safety Monitoring Plan. In brief, we will monitor participants based on their answers to a survey question about whether their employer has treated them unfairly. Overall, approximately 6% of participants in the observational Breast Cancer and the Workforce study said they thought their employer had treated them unfairly. In the current study, we will call each participant who takes the 4-month survey and says her employer treated her unfairly. In the call, we will ask about the circumstances that led to this negative outcome. If there are 10 cases (per arm, at any time during the study) for whom the negative outcome is attributable to the app or booklet, we will stop the study. During the monitoring process, we will revise the intervention as needed.Failure to report a significant symptom to the clinic teamThe intervention that will be evaluated in this study includes information about common treatment-related symptoms. Additionally, patient reported symptoms will be assessed in participant surveys. The study team will not relay information about participants’ symptoms to the clinic team. Instead, participants will be expected to report any symptoms *directly* to their oncology providers. During the consent discussion participants will be informed that the information collected from them as part of the study is for research purposes only and will *not* be shared with the clinic team as part of their routine care. Furthermore, prior to initiating each survey participants will be reminded of the importance of communicating directly with the clinic team and relaying any information about symptoms directly to the appropriate physician or nurse. However, if a member of the research team or a nurse reviewer identifies an active and serious problem for a patient that should be addressed by a healthcare provider, he or she will notify the patient’s physician.Transitory distress related to thoughts about breast cancerThe risk of mild transitory distress prompted by the study intervention, control (informational brochure), usability testing, and surveys will be mitigated in several ways. First, all study materials will use clear and simple language and adhere with expert recommendations for surveys and interventions. Second, participants will be provided with contact information for the study investigators and the institutional review board at that subject’s recruitment site. All study staff who will interact with participants (i.e. in the consent process, through interviews, or when approaching participants due for surveys in clinic) will be trained in the protection of human subjects and will receive additional study-specific training to recognize and reduce participant distress. Any participant who feels distressed at any point will have the option to terminate study participation. We believe that the risk of distress due to study procedures in this in this study is low and if present, will be only mild and transitory. All research staff will be trained to identify signs of psychological discomfort in the participants. Any patient reporting significant distress (or indicating distress through other signs) will be referred to a licensed or board-certified mental health provider for additional evaluation, support, and/or referrals as needed.Breach of confidentialityAll data files will be password-protected and stored on secure servers in the Department of Psychiatry and Behavioral Sciences at Memorial Sloan Kettering Cancer Center. Access will be restricted to personnel working directly on this project. Files that must be shared with the rest of the study team or research coordinators will be shared using MSK’s secure file transfer system. Any printed data will be stored in a locked file cabinet and will be destroyed when no longer needed. Patient identifiers will be used to link information from multiple sources. We will assign patients a random number for data analysis. The matched list of patients and random study numbers will be kept by a member of the research team in a password-protected file. No attempt will be made to identify individual patients or providers beyond the use specified in this study. Publications and presentations of the data will adhere to all requirements for the protection of patient privacy and confidentiality, and no patient or provider will be individually identifiable. All data will be presented in aggregate form.

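### The harm-stopping rule is meant to run throughout the study, but the only case-finding route described is the 4-month post-treatment survey, so harm during treatment is counted late or missed

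*Protocol article*

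**What the plan says.** The Protocol article, Interim analyses {21b}, states the purpose: "We have incorporated monitoring and a standalone early stopping rule to ensure the app is not causing harm". It gives a background figure: "Overall, approximately 6% of BCW study [7] participants said they thought their employer had treated them unfairly". Cases are found as follows: "we will call each participant who takes the 4-month survey and says her employer treated her unfairly". Staff ask about the circumstances, and the boundary is "If there are 10 cases (per arm, at any time during the study) for whom the negative outcome is attributable" to the app or the booklet. The next sentence allows the intervention to be revised as monitoring proceeds.

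Adverse event reporting and harms {22} repeats the rule ("we will monitor participants based on their answers to a survey question about whether their employer has treated them unfairly") and again names only the 4-month survey for the call. It presents this as a summary and refers to the research plan and the Data and Safety Monitoring Plan for more detail.

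The Post-treatment surveys section places the survey 4 months after chemotherapy, surgery and radiation are all complete. Of the two surveys taken during chemotherapy, the On-treatment surveys section says: "These surveys will include an assessment of symptoms, accommodations, work status, and the two measures of self-efficacy". No question on unfair treatment is listed there.

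**The concern.** The harm that the rule guards against is an employer's adverse reaction to a request for accommodations. The app is meant to help women negotiate and keep working during chemotherapy, so many of these requests, and some of the reactions, should come before active treatment ends. The rule nevertheless takes its cases from a survey given 4 months after that point. The wording of the boundary implies continuous counting, but no earlier data source is described.

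Two things are at stake. First, cases that arise during treatment reach the count months later, while more women are being enrolled, and women who never complete the 4-month survey have no described way into the count. Second, ten attributable cases is a high count against the protocol's own background rate, so the delay matters more.

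**Working it through.** **Inputs from the Protocol article.** Boundary: 10 attributable cases per arm (Interim analyses {21b}). Background rate of unfair treatment from any cause: about 6% (same section). Evaluable at 4 months: 167 per arm. Enrolment: 420 in total, 1:1, so 210 per arm (Sample size {14}; Trial design {8}).

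**Inputs assumed.** The RCT start date, the accrual rate and the time from enrolment to the 4-month survey are not given. I took uniform accrual over 18 to 30 months and a lag of 8 to 12 months. The adherence section ({11c}) expects most women to have finished chemotherapy by 8 months after enrolment, and the survey comes 4 months after the last active treatment.

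**Reproducing the plan's sample size.** The plan states: "we would require 167 evaluable participants in each arm based on a 2-sided test with a 5% type I error and 80% power". For 50% against 65% with unpooled variance, n = (1.960 + 0.842)² × (0.50×0.50 + 0.65×0.35) / 0.15² = 166.6, so 167 per arm. This matches. The share of enrolled women expected to supply 4-month data is 334/420 = 79.5%, so about one in five does not.

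**Step 1: boundary against background.** Expected all-cause reports in a full arm: 0.06 × 167 = 10.0. Completers needed on average for ten cases at 6%: 10/0.06 = 166.7, which is the whole evaluable arm.

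**Step 2: chance that the boundary is ever reached.** With X binomial(167, q), where q is the rate of attributable cases:

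| q | P(X ≥ 10) |
|---|---|
| 3% | 0.03 |
| 4% | 0.13 |
| 6% | 0.55 |
| 8% | 0.87 |
| 10% | 0.975 |

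With 85% retention (0.85 × 210 ≈ 178 completers), the values at 6% and 8% become 0.63 and 0.91.

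**Step 3: when it is reached.** The expected share of enrolment complete at the tenth case is (10/q)/(210 × 0.8) + lag/accrual, capped at 100%.

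- q = 6%: 166.7/168 = 0.99 before any lag is added, so 100% in every setting.
- q = 10%: 100/168 = 0.595. With a lag of 8 and accrual of 30 months, 0.595 + 0.267 = 0.86. With 8 and 24, 0.595 + 0.333 = 0.93. With 12 and 18, it passes 1. Range: 86% to 100%.
- q = 18%: 55.6/168 = 0.331. With 8 and 30, 0.331 + 0.267 = 0.60. With 12 and 18, 0.331 + 0.667 = 1.00. Range: 60% to 100%.

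A simulation over the same grid (4,000 runs per setting) agrees. Median enrolment at the tenth case was 100% in every setting at 6%, 75% to 100% at 12%, 59% to 99% at 18%, and 46% to 86% at 30%. At 6%, the chance of reaching the boundary before enrolment ended was 0.2% to 19%.

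**The case against.** The strongest reply is that the article says it is summarising. The harms section refers to a Data and Safety Monitoring Plan that is not shown, and denominators, arm-level tables and operating characteristics may be set out there. That stands, and their absence from the article is not held against the plan.

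Nothing in the text excludes cases from other sources. Women who report work-related repercussions are to be referred to counseling or legal help, with no survey or time limit. However, the text does not say that such cases count toward ten. Survey content lists in an article may also be incomplete: the post-treatment list omits the unfair-treatment question too, although the stopping rule shows that it is asked at 4 months. So the on-treatment list alone does not prove that the question is never asked earlier. But both descriptions of the rule name only the 4-month survey for the call that establishes attribution.

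Other safeguards exist. The intervention may be revised before ten cases, though no trigger is set. The institutional monitoring section describes committee review through the study's life, participants with significant study-related distress are removed, and the consent waiver rests on minimal risk. Because each case is attributed after a call, an absolute cap without a between-arm test is a defensible choice. Requests and reactions can also occur after treatment, when a post-treatment survey suits them.

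A reader might infer that the rule can act only once enrolment is nearly complete, that moderate harm would probably never trigger it, or that women still enrolling have almost no protection. The documents do not support these readings. Large harm could reach the boundary well before full enrolment. A low chance of ever reaching it applies only to attributable rates below about 6%. The safeguards above also count for something.

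**Conclusion.** The concern holds as a mismatch between a rule said to operate throughout the study and the single, late survey described as feeding it. The mismatch stands on the text alone. Harm during treatment is found late, and by the described route not at all in about one fifth of women.

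The probabilities of ever reaching ten rest on the protocol's 167 responders per arm and on independent cases. The 6% benchmark covers any cause, while the rule counts only attributed cases. The timing figures depend on the assumed accrual and lag and should be read as ranges. Since the trial is minimal risk and the repair is cheap, this should be corrected, but it does not undermine the primary analysis.

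**What to change.** Ask the unfair-treatment question at every scheduled survey, including mid- and end-of-chemotherapy, and make the follow-up call each time it is answered yes. State that cases found this way, or reported spontaneously and attributed after a call, count toward the rule, so that case finding matches the stated scope. Give the monitoring committee cumulative attributed and all-cause reports over respondents, by arm, together with the probabilities above, so that it can confirm the threshold knowing how the rule behaves. No particular threshold is proposed here. If the Data and Safety Monitoring Plan already does any of this, a sentence in the protocol saying so is enough.

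The cost is one added item in existing surveys, more calls by existing staff, and one table by arm for the committee. The primary endpoint and its analysis do not change.
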